**Methods:**

A randomized, controlled clinical trial in 58 women with post-mastectomy lymphoedema. The control group includes 29 patients with standard treatment (skin care, exercise and compression measures, bandages for one month and, subsequently, compression garnments). The experimental group includes 29 patients with standard treatment plus Manual Lymphatic Drainage. The therapy will be administered daily for four weeks and the patient's condition will be assessed one, three and six months after treatment.

The primary outcome parameter is volume reduction of the affected arm after treatment, expressed as a percentage. Secondary outcome parameters include: duration of lymphoedema reduction and improvement of the concomitant symptomatology (degree of pain, sensation of swelling and functional limitation in the affected extremity, subjective feeling of being physically less atractive and less feminine, difficulty looking at oneself naked and dissatisfaction with the corporal image).

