### Treatment groups

#### Group A or Control Group

Ambulatory treatment is performed for one month. Specific exercises and prevention measures are taught. In the first four weeks, multilayer bandage is applied daily. Bandaging consists of a first layer of cotton (Velband) followed by protection at the points of support and a bandage of low elasticity (Comprilan) of different widths (six centimeters for the area of the hand and eight centimeters for the rest of the extremity).

The tailor-made sleeve for lymphoedema with a gauntlet without protection at the edges and with extension to the shoulder is applied for the first four weeks of treatment. The sleeve is used all day, and at night interruption is allowed. Later on, the patient will continue domiciliary treatment, performing specific exercises for 30 minutes twice a day without experiencing fatigue, and wearing the lymphoedema sleeve for at least 12 hours.

If after three months of treatment a satisfactory response is not achieved, an ambulatory treatment will be re-established for one month, and this time the experimental treatment (group B) will be used.

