#### - Group B. Experimental group

Ambulatory treatment is carried out for one month. Specific exercises and prevention measures are taught. In the first four weeks, MLD is applied followed by a daily multilayer bandage. The bandage consists of a first layer of cotton (Velband) followed by protection at the points of support and a bandage of low elasticity (Comprilan) of different widths (six centimeters for the area of the hand and eight centimeters for the rest of the extremity). The tailor-made sleeve for lymphoedema with a gauntlet without protection at the edges and with extension to the shoulder is applied for the first four weeks of treatment. The sleeve is used all day, and at night interruption is allowed. Later on, the patient will continue domiciliary treatment, performing specific exercises for 30 minutes twice a day without experiencing fatigue, and wearing the lymphoedema sleeve for at least 12 hours.

If after three months of treatment a satisfactory response is not achieved, an ambulatory treatment will be re-established for one month, and this time the treatment corresponding to group A or control group will be applied.

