### Outcomes

#### Primary Outcome

Volume reduction of lymphoedema in the affected arm after treatment, expressed as a percentage. The condition is considered to be lymphoedema when there is a difference of at least 200 ml between the volume of the affected arm (measured by circometry and calculated using the formula of the truncated cone) and the volume of the contralateral arm. A response is considered to be good when a reduction of at least 20% of the volume is achieved after the treatment of lymphoedema in the affected extremity compared to baseline. These measurements will be performed at the beginning of the study, after the first and third month and after six months of follow-up. The volume difference has been used for the predetermination of the sample size.

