### Interventions and distribution of tasks

The rehabilitation physician's functions include:

1. Selection call: the physician determines whether the patient meets inclusion criteria and if so, she is randomized into a treatment group. He/she carries out a complete medical history (history and complete physical exam, taking measurements of both upper extremities for the calculation of lymphoedema volume). He/she explains and provides the informed consent and collects the signed copy. He/she gives the quality of life questionnaire to the patient, who will complete it before starting the outpatient treatment.

2. Week 2 of treatment: Examine the patient. Take measurements of the upper extremities. Rule out the existence of treatment-related side effects. Make the request for a lymphoedema garment. Collect the quality of life questionnaires.

3. Week 5 of treatment: Examine the patient. Take measurements of the upper extremities. Rule out the existence of treatment-related side effects. Check the sleeve. Give a compliance diary to the patient.

4. Week 12 of treatment: To examine Explore the patient. Ask about possible complications that may lead to withdrawal from the study. Take measurements of both upper extremities. If the response to the treatment is good, the patient will be encouraged to continue complying with treatment. The patient's diary is reviewed. A second quality of life questionnaire is provided. The treatment is continued at home. If the response to the treatment is poor, the patient is included again in an outpatient treatment for a month so that if the patient has previously received TH now he/she would be treated with TH + DL and if he/she has been previously treated with TH + DL now she would be treated with DL. The patient is examined at week 16. Measurements of the upper extremities are taken. The presence of treatment-related side effects is ruled out.

5. Week 18 of treatment: the patient is examined. Measurements of the upper extremities are taken. The presence of treatment-related side effects is ruled out. The sleeve is reviewed. A second quality of life questionnaire is delivered.

6. Final call: Week 24 of treatment: the patient is examined. The patient is asked about possible complications that may lead to withdrawal from the study. Measures are taken in both upper limbs. The sleeve is reviewed.

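### The week-12 rule re-treats group B poor responders with DL, which contradicts the group B section and matches no regimen the article defines; very probably a slip for TH

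*Protocol article*

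**What the plan says.** The Protocol article gives the re-treatment rule for poor responders in two places.

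- **Treatment groups.** Each arm's description ends with what happens if the response after three months is not satisfactory: one further ambulatory month on the other arm's treatment. For group A: "and this time the experimental treatment (group B) will be used". For group B: "this time the treatment corresponding to group A or control group will be applied".
- **Interventions and distribution of tasks, rehabilitation physician, week 12.** Poor responders return to outpatient treatment for a month. For those who began on the control treatment: "if the patient has previously received TH now he/she would be treated with TH + DL". For those who began on the experimental treatment: "if he/she has been previously treated with TH + DL now she would be treated with DL".

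The Methods part of the abstract defines the two arms. On control: "The control group includes 29 patients with standard treatment (skin care, exercise and compression measures", followed by bandages for a month and then garments. On the experimental arm: "The experimental group includes 29 patients with standard treatment plus Manual Lymphatic Drainage". The article does not expand TH or DL anywhere.

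**The concern.** Both places describe the same patients (group B, poor response), the same decision (three months, or week 12) and the same course (one outpatient month). One prescribes the control treatment, the other DL. Both cannot be right.

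The week-12 text is not background. It is the physician's instruction for the visit at which the decision is made, and the physiotherapist then applies what has been prescribed. If it were followed to the letter, re-treated group B patients would receive the component that the group B section removes, and would not receive the outpatient course that the group B section assigns. A reader of the six-month results also needs to know what these patients had between months 3 and 6, and the article gives two answers.

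**Working it through.** The check is textual. No figure in the plan depends on this rule, so there is none to reproduce.

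**Step 1: decode the abbreviations.** Set the group A halves of the two statements side by side.

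| Source | First treatment | Re-treatment |
|---|---|---|
| Treatment groups, group A | control | group B (experimental) |
| Week-12 rule, first half | TH | TH + DL |

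These agree if TH is the control treatment and TH + DL the experimental one. The abstract defines the experimental arm as standard treatment plus manual lymphatic drainage, so TH is the standard treatment and DL is the added drainage.

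**Step 2: apply the decoding to group B.**

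| Source | First treatment | Re-treatment |
|---|---|---|
| Treatment groups, group B | experimental | group A (control), that is TH |
| Week-12 rule, second half | TH + DL | DL |

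The re-treatment cells differ. DL without TH is drainage without the standard treatment.

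**Step 3: ask whether DL alone could be meant.** The article defines two regimens, standard treatment and standard treatment plus drainage. It describes no drainage-only regimen. Replacing the final DL with TH makes the week-12 rule agree with the group B section and restores the symmetric switch. The other one-term repair, reading TH + DL again, would leave the patient on the treatment that had just failed and would still contradict the group B section. TH is therefore much the more likely intended word.

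**Step 4: what the literal wording changes.** The rule concerns the outpatient month. The group A outpatient course includes daily multilayer bandaging. The clear literal effect is drainage in place of that course.

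**Step 5: scope, by counting.**

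- Patients: at most the 29 of 58 randomized to group B. The number of poor responders among them is not given.
- Measurement visits after baseline for a re-treated patient: weeks 2, 5, 12, 16, 18 and 24, which is 6. After the week-12 decision: weeks 16, 18 and 24, which is 3 of 6. The week-16 visit is written within the poor-response branch ("The patient is examined at week 16. Measurements of the upper extremities are taken"), so this count need not apply to patients who are not re-treated.
- Time points named for the primary outcome: "after the first and third month and after six months of follow-up", that is 3 after baseline. Only month 6 follows the decision, 1 of 3. The month-3 value is taken at the decision visit, before any re-treatment begins.
- Sample size: the calculation uses mean reductions of 5% and 25%, a standard deviation of 25%, alpha 0.05, power 0.80 and 30% dropout. None of these inputs involves the re-treatment rule.

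**The case against.** The strongest reply is that the article resolves the matter itself. The Treatment groups section is where the interventions are defined, it states the switch symmetrically and in full words, and the task list is later shorthand. On that view this is an editorial slip with an obvious correct reading. Much of this stands: the intended meaning can be recovered, and the point is minor. It does not remove the error, because the shorthand is the instruction for the decision visit, its terms are undefined, and it says something different from the defining section.

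A second reply is that a condensed article does not show which working text the staff use. That is right, and it rules out any claim about what patients received. It does not excuse two conflicting statements of one rule in the same article.

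Two stronger readings are tempting and are not supported:

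- A reader might infer that group B poor responders lose skin care, exercise and compression altogether for a month. The week-12 rule names only the outpatient treatment. The group B section has home exercise and at least 12 hours of daily sleeve wear continuing after the first month, and no text stops them. The sleeve is reviewed at weeks 18 and 24 with no exception for re-treated patients.
- A reader might infer that this word is what compromises the six-month comparison. The planned switch of poor responders in both arms already mixes the regimens by month 6, whichever word is used. Correcting the word makes the re-treatment a defined regimen; it does not undo the mixing.

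**Conclusion.** Wrong as written, and minor. The week-12 rule gives re-treated group B patients DL, against the control treatment in the group B section, and DL alone corresponds to no regimen in the article. That it is a slip for TH is an inference, because the abbreviations are undefined. It rests on the parallel with group A, the explicit wording of the group B section and the absence of any drainage-only regimen.

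The consequence is confined to what re-treated group B patients receive before weeks 16, 18 and 24, and so to the six-month point among the primary outcome's time points. This assumes that the third-month measurement is the one taken at week 12. Months 1 and 3, the sample size and the power do not change. No effect size, patient count or actual mistreatment is claimed.

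**What to change.** Reword the week-12 rule so that it names the regimens. For example: a patient with a poor response who was first treated in group A receives the group B treatment (standard treatment plus manual lymphatic drainage) for one month; a patient first treated in group B receives the group A treatment (standard treatment alone) for one month.

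Swapping the final DL for TH would remove the contradiction but leave two unexplained abbreviations in a treatment rule, so TH and DL should be replaced or, if kept, defined at first use. The investigators should confirm that the group B section states what was intended, and make the same correction in any working document that carries the week-12 wording.

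The cost is one sentence of text, with no extra patients, visits or data.

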### Ethical Approval

The study was approved by the Hospital Ethical Committee (Comite Ético de Investigación Clínica (CEIC) FIB Hospital Universitario de la Princesa) and will be conducted in accordance with the declaration of Helsinki.

## Discussion

### Relevance of the project in terms of its impact in clinical care

Within the Complex Physical Therapy (CPT), it is relevant to know how useful the Manual Lymph Drainage is because of the exclusive dedication of the therapist and the number of sessions required to complete this portion of the treatment. If it is proven to be effective, more staff trained in this technique should be provided to health centres so that affected patients can have access to it easily.

### Relevance of the project in terms of its bibliometric impact

The systematic review of literature on the management of lymphoedema was limited by the lack of prospective randomized trials evaluating different treatment options. In 2006, a Cochrane systematic review about physical treatments for reducing and controlling lymphoedema of the extremities selects only three of the articles reviewed on the basis that they are randomized controlled trials that had a follow-up period of at least six months. However, because they did not study the same treatment intervention, the data could not be subsequently pooled. Some evidence suggests that treatment involving a combination of MLD and compression therapy yields reduced oedema volume compared to compression therapy alone if volume is measured directly after the conclusion of MLD (Evidence grade 3 = limited scientific evidence). The existing randomized clinical trials are conducted with small samples and only a few studies include long term monitorization. None of the studies performed are blind and only rarely is an analysis of the rate of "lost to follow-up" patients performed. Before this therapy can be recommended, more randomized controlled trials with an adequate sample size, where MLD short-term and long-term treatment effects could be more closely studied, are needed (SBU Alert Report 2005-04. http://www.SBU.SE/ALERT).

Moreover, groups of experts have highlighted the lack of interest in researching the impact of the physical and psychosocial difficulties of these patients and their quality of life. In conclusion, the need for performing well-designed, randomized trials of the physical treatments and their health impact is a priority.
